## Measurements

### Students

#### Questionnaire

A comprehensive set of standardized questionnaires is being filled in by all participants (Table 1).

**Table 1 Tab1:** Outcome measures

Outcomes	Informant			Measurement
	Student	Teacher	Parent	
Mental Wellbeing				
*Primary outcomes*				
Resilience, resilience scala (RS14)	x			
Existence or absence of depressive symptoms (RBDI)	x			
Experienced psychological strenghts and difficulties (SDQ)	x	x	x	
*Secondary outcomes*				
Mindfulness (CAMM)	x			
Happiness (OECD Better life Index)	x			
Satisfaction with life (SWLS-C)	x			
Quality of life (KINDL-R)	x		x	
Positive and negative affects (PANAS)	x			
The Rumination-Reflection Questionnaire				
Stress in Children (SIC Qestionnaire)				
Compassion/self-kindness)	x			
Cognitive measuments				
NEPSY-II (Developmental Neuropsychological Assesment)				x
WISC-IV (Wechsler Intelligence Scale for Children)				x
D-KEFS (Delis-Kaplan Executive Function System)				x
Psychological flexibility (CERQ)	x			
Viivi, 5-15 questionnaire on child development			x	
Psycho-physiological responses				
SCR (Skin conduct response)				x
EKG (Electrocardiography)				x
Academic achievement/school				
Grade average in the last school report	x	x		
Grades in last school report	x	x		
Satisfaction with ow achievements	x			
Days of absence from school		x		
Bullying at school	x			
Health behavior in school-aged children, WHO HBSC				
Physical activity	x			
Sleeping/tiredness	x			
Alcohol use	x			
Smoking	x			
Screen time	x			
Motivational determinants of practice				
Outcome expectations	x			
Use of strategies to relax	x			
Self-efficacy	x			
Intention/motivation	x			
Class room social environment (CES)	x	x		
Personality inventory (TIPI)	x			
Psycho-social background factors				
Experienced major difficulties in life	x			
The quality of social relationship with peers	x			
Major changes in student's life			x	
The emotional athmospere at home	x		x	
The relationship with mother	x			
The relationship with father	x			
Socio-demopraphic background factors				
Financial situation in the family	x			
Family composition	x			
Mother tongue	x		x	
Parent education			x	
occupation			x	
Employment status			x	

Students fill in their questionnaires at school under facilitators’ or teachers’ monitoring. Parents fill in their questionnaires at home and bring/send them to school in a closed envelope. Teachers fill in their questionnaires during their working hours at school, if possible. The filled questionnaires (students, teachers, parents) are collected from schools and brought to recording company’s premises approximately 2–3 weeks after the intervention period has finished.

##### Primary outcomes

In children’s and adolescents, existence or absence of depressive symptoms was measured with the Finnish version of the Beck Depression Inventory (RBDI) [57]. The well-being was measured with the Strenghts and Difficulties Questionnaire (SDQ) [58]. The resilience was measured with Resilience Scale (RS14) [59] that has shown good internal consistency reliability among adults, Cronbach Alpha (CA) 0.87 [60]. The Finnish versions of SDQ [61], Cronbach Alpha (CA) 0.71 and RBDI [62, 63] CA 0.83, 0.87 have shown adequate psychometric properties among youth.

##### Secondary outcomes

The secondary outcomes of the present study are conceptualized as children’s and adolescents’ cognitive–emotional factors that are essential for their resilience, mental health and well-being; Mindfulnesss, Happiness, Satisfaction with Life, Quality of Life, Positive and Negative affects, and compassion/self-kindness, the rumination, and stress. Additionally cognitive functions, psychophysiological responses, academic achievements, health behavior, and motivational determinants of practice have been included in the present study (Table 1).

##### Psycho-physiological and neuropsychological measures

Both the objective neuropsychological and psychophysiological measures were collected from a subset of students: 62 students in the intervention group and 69 students in the control group (relaxation programme) were randomly selected from four 6th grade and four 8th grade classes (*N=*131). There were three measurement points: before the intervention started , directly after the intervention period, and 6 months after the intervention period. Neuropsychological tests include subtests from NEPSY-II [64], WISC-IV [65] and D-KEFS [66].

*NEPSY-II* [64] (Developmental Neuropsychological Assessment) is a series of neuropsychological tests, used in various combinations to assess neuropsychological development in children [64]. In this study we will administer the test of *Inhibition*, measuring the ability to inhibit and switch response types, which is a part of the attention and executive functioning domain category.

*WISC-IV* (Wechsler Intelligence Scale for Children) is a well-known and widely used assessment of cognitive functioning in children [65]. We administer the *Working memory* subtest, which assesses the ability to hold and manipulate new information in the short-term memory.

*D-KEFS* (Delis-Kaplan Executive Function System) is set of neuropsychological tests used to measure variety of verbal and non-verbal executive functions [66]. The subtests to be administered include the *Trailmaking test* (measuring flexibility of thinking on a visual-motor sequencing task) and the *Verbal fluency test* (measuring letter, category and category switching fluency).

##### Psycho-physiological measures

The psycho-physiological measurement will be conducted with the mobile Nexus instruments from the psychology laboratory in Helsinki University. The measurement includes skin conductance response, heart rate and electrocardiography.

Skin conductance response [67] method for measuring the electrical conductance of the skin which varies with moisture level. Sweat glands are controlled by the sympathetic nervous system, so skin conductance is used as an indication of psychological or physiological arousal. Therefore, if the sympathetic branch of the autonomic nervous system is highly aroused, sweat gland activity will also increase, which in turn increases skin conductance. In this way, skin conductance can be used as a measure of emotional and sympathetic responses. A pair of electrodes is attached to palm or fingers to measure the response over a period of time.

Electrocardiography is a transthoracic interpretation of the electrical activity of the heart over a period of time, as detected by electrodes attached to the surface of the skin and recorded by an electrocardiogram [68]. The electrical activity of the heart is sensitive to the changes of a range of bodily functions, such as effects of the autonomic nervous system, metabolism and hormonal influences (Table 1).

### Measurement procedure

Instruments are placed in a classroom, where the students can come in groups of 3. The measurement will take approximately 1 h/student. At first there will be the basal or resting measurement. After that students will be presented two stress inducing tasks. The first task is a mathematical problem (cognitive stress) and the second task is a small speech given to the researcher, research assistants and others students (social stress). Speech task is divided to three parts, so each student has the opportunity to give their speech on a novel subject, while others listen.

### Teachers

The teacher rated secondary outcome measures include experienced psychological strengths and difficulties measured by Strengths and Difficulties Teacher Form [58], and classroom social environment measured by Classroom Environment Scale [69]. In addition to these, in 6 months’ follow-up teachers were asked to assess the pedagogical and beneficial elements of the intervention and control programs both to their students, as well as their own work load and work satisfaction (Table 1).

### Parents

Parents were asked background information regarding their education, sufficiency of their salary to necessary expenses, athmosphere at home, major life changes (of their child attending the study or the whole family) and experienced psychological strengths and difficulties measured by Strengths and Difficulties Parent Form [58]. Apart from the background information, a description of all measures used in the data collection is reported in Table 1.

### Long run follow- up

In addition to 6 and 12 months follow-up, a linkage to main health, or health related, registers will be done (The Social Insurance Institution of Finland; National Institute for Health and Welfare; Statistics Finland).

### Intervention

A 9-week mindfulness intervention program .b (Stop & Breathe) [46] is designed to teens aged 11–18 years by experienced classroom teachers and mindfulness practitioners with researchers from the Oxford, Cambridge and Exeter universities. The program consists of nine 45-min group sessions and mindfulness home practices designed to improve emotional awareness, sustained attention, and attentional and emotional regulation. The program is standardized, highly recognized; and the preliminary research, though based on small intervention populations, suggests that it is effective [49].

### Active control intervention

The control group receives a standardized relaxation program called “Relax” developed in co-operation with Folkhälsan Förbundet (based on program called “Chilla”). Relax-program aims to produce relaxation skills and holistic wellbeing for the control group attendants. Every lecture is divided in two parts, relaxation exercises and group discussion about different topics, e.g., stress, relaxation, upsides and downsides of smartphones, sleep, excercising, food and attitudes. Relaxation includes progressive muscle relaxation, a breathing excercise, visualization, choose your emotion for rest of the day and short brake for regaining energy. The dose of the program is the same as in the .b intervention, i.e. nine 45 min group sessions and home practices.

### Non-treatment control intervention

The third arm, non-treatment-group will fill-in the same research questionnaires during the same time periods as the intervention and control groups (except the short questionnaire after the 5th lesson) in spring 2015 and in spring 2016 (ongoing). The non-treatment group will receive a shorter well-being course after the one year follow-up has been conducted.

### Pilot intervention study

The acceptability and feasibility of the program has been ensured in a previous controlled pilot intervention study in two schools (4 classrooms with 19–22 students each, altogether 82 participants). The study was conducted in autumn 2012 and it indicated suitability and fit of the program to the Finnish educational system, students and staff. A qualitative assessment and the quantitative calculations showed promising effects on pupils’ executive skills and well-being. Quantitative analysis showed differences between genders; among girls the greatest benefits were seen in improved self-esteem (*p* = 0.008) and stress resilience (*p* = 0.014), whereas among boys in improved self-awareness (*p* = 0.006).

### Treatment fidelity

The program is delivered by 14 educated facilitators. All facilitators were provided with a self-monitoring sheet which are used for the self-assessment of their performance (e.g. intention, attitude, ability to be mindful and conduct the lesson with empathy and kindness) as well as to guarantee that the core elements of each lesson are delivered. The facilitators also assess the student’s behaviour and ability to receive and internalize the core elements of a given .b lesson, as well as the teachers’ presence at lessons and attitudes toward the program.

Before the intervention data collection was launched, each facilitator conducted a randomly selected .b lesson that was assessed both quantitatively and qualitatively by research group members and collagues who have attended a mindfulness-based stress reduction course but who are not part of the present research group. These lessons were also videotaped, as well as the mentioned assessment discussion. This procedure was conducted to guarantee that all facilitators are conducting “the same program with the same intention”. Out of the 14 facilitators, all nine intervention group facilatators have attended a 8-week mindfulness-based stress reduction course, are educated in delivering .b school program, and practice mindfulness in their own lives. All facilitators, including active control group facilitators, except one, have received their basic education either in education or health and welfare, consisting of teachers (5), psychologists (2), health professionals (5), nutritionist (1), and a lawyer (1).

## Sample size

The sample size was estimated to detect the mean difference of 0.2 standard deviation units (effect size = 0.2) on main outcomes of risk for depression (RBDI), social/emotional/behavioural skills (SDQ) and resilience (RS14) between intervention and control groups with 80 % power and the two-tailed 5 % level of significance. The clustering of outcomes within schools was taken into account, assuming an intra-cluster (intra-school) correlation coefficient of 0.03 and assumed that on average 60 children in each school will complete the study. The required sample size was estimated to be 1090 children per group, and allowing for about 10 % drop-out rate, the study requires 1200 children per group and total of 2400 children to be recruited. On the RBDI and SDQ total difficulties score, an effect size of 0.2 corresponds to a mean decrease of 0.8 score on the RBDI scale and a mean decrease of 1.0 score on the SDQ scale, assuming the standard deviations of 4 for RBDI [62] and 5 for SDQ [61]. The effect size of 0.2 corresponds to a mean increase around 2.5 score on the resilience scale, assuming the standard deviation of 13 [70].

In addition to comparing the intervention and control groups, we were interested in comparing the intervention and non-treatment groups in order to gain even more strength into the study design. However, this was not our primary intrest. Since the previous research has shown also standard relaxation programs to have beneficial effects on well-being, we are expecting to find greater differences between intervention and non-treatment groups compared to intervention and control groups. Using the same assumptions to detect the mean difference of 0.3 standard deviation units (effect size of 0.3) between intervention and non-treatment group, the required sample size was estimated to be 486 children per group, and allowing for about 10 % drop-out rate, the study requires 540 children in the non-treatment group.

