### Randomization procedure

The recruitment started by listing all the schools in a Southern part of Finland. After choosing the schools (including as many classes of the same grade as possible), a letter explaining the study procedure was sent by e-mail to the head masters. Within few days after sending the information letter, the research team members called the headmasters by telephone. In most schools the decision to take part to the study was made collectively by the head master and the class teachers (of the chosen grades). The schools were enrolled from 14 cities/municipalities during the collection of the data (years 2014–2016). Altogether 247 schools were contacted, 59 of those participated in the study participation percentage being 24. In each municipality we aimed at an equal number of intervention and control classes. In order to achieve balanced intervention and control groups, schools participating in the study were randomized using the available background variables. The selection of intervention-control pairs was primarily based on the language being used for teaching (Finnish, Swedish or English, the grade, the school location, the number of classes participating in the investigation and, if necessary, the average apartment price per square meter in the school’s neighborhood).

The classes were randomly assigned to mindfulness intervention classes (*N* = 85) and control classes (*N* = 79) and non-treatment classes (*N* = 28). Due to practical reasons, in spring 2014 and in autumn 2015 schools were divided into two arms (intervention and control) and in spring 2015 and spring 2016 into three arms instead of two: intervention, control and non-treatment groups. First, the schools were divided into three groups based on the school location and the average apartment price per square meter. Within each of these groups, the total number of schools and classes varied. Next, the schools for these groups were divided into three subgroups including approximately same number of classes (some schools were combined into one subgroup to achieve an as even distribution of classes as possible).

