### Data collection timeline

The data from intervention and control groups have been collected during four academic terms: In the beginning of spring term in 2014 (*N* = 523), in the beginning of autumn term in 2014 (*N* = 1090), in the beginning of spring term in 2015 (*N* = 821), and in the beginning of spring term in 2016 (on going, baseline including *N* = 203). Hence the last follow-up will be collected in spring 2017 (12 months follow-up of the spring 2016). Among intervention and control groups data have been collected at baseline, in the middle of the intervention (the fifth week of the intervention, a short formula), within 1 week after the intervention, and 6 and 12 months after baseline from the same participants.

Due to practical reasons, the data from non-treatment group have been collected during two academic terms: In the beginning of spring term in 2015 (*N* = 254), and in the beginning of spring term 2016 (ongoing, baseline including *N* = 109). Additionally, non-treatment group did not fill in the short formula in the middle of the intervention the measurement points being otherwise identical with the other two groups (incl. follow-ups).

Among teachers and parents data have been collected at baseline, after the intervention and 6 months after the baseline from the same parent (if only one parent filled-in the formula) and from the same teacher. In a case the teacher had left/changed between the different measurement points, only the grades and absence from school of students were asked (from the new teacher).

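### The non-treatment arm is planned at 540 children but the article's own baseline counts give 363, and the shortfall and its effect on power are not stated

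*Protocol article*

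**What the plan says.** The Sample size section gives the mindfulness versus non-treatment contrast its own calculation. The target is to "detect the mean difference of 0.3 standard deviation units (effect size of 0.3) between intervention and non-treatment group". The other inputs are carried over from the main calculation: "with 80 % power and the two-tailed 5 % level of significance", "assuming an intra-cluster (intra-school) correlation coefficient of 0.03", and the expectation that "on average 60 children in each school will complete the study". From these, "the required sample size was estimated to be 486 children per group", and after about 10% loss the "drop-out rate, the study requires 540 children in the non-treatment group". The same section says that this contrast is not the main interest of the trial.

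The Data collection timeline says that "the data from non-treatment group have been collected during two academic terms": 254 children in spring 2015 and 109 in spring 2016, the latter marked as ongoing. The Randomization procedure says that schools were divided "in spring 2015 and spring 2016 into three arms instead of two", and into two arms in the other terms.

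The Analysis plan says that all randomised classes are analysed in their assigned groups. It does not say whether the non-treatment contrast uses intervention classes from every term or only from the two three-arm terms. The abstract names the non-treatment group within the primary aim.

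**The concern.** A required size and the numbers recruited stand in the same article, differ by 177 children, and are not connected by any comment. A reader of the Sample size section alone would take the non-treatment contrast to have 80% power at 0.3 SD. If the result is null or imprecise, it would be read against a level of power that the randomised comparison does not have under the plan's assumptions. The abstract adds to this by placing the contrast inside the primary aim, although the Sample size section gives it lower standing.

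**Working it through.** **Inputs from the article.** Effect 0.3 SD; two-sided 5%; 80% power; ICC 0.03; 60 completers per school; 10% drop-out. Non-treatment baseline counts are 254 and 109. Intervention plus control counts in the same two terms are 821 and 203, and over all terms 523, 1,090, 821 and 203. There are 59 schools.

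**Inputs assumed.** The article does not split the intervention plus control counts by arm within a term, so half are taken to be intervention. It does not give schools per arm, so these are taken as completers divided by 60.

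**1. The plan's own figure reproduces.**
- Design effect: 1 + 59 × 0.03 = 2.77.
- Unclustered size per group: 2 × ((1.96 + 0.8416)/0.3)² = 174.4, rounded up to 175.
- With clustering: 174.4 × 2.77 = 483, or 175 × 2.77 = 485. The article states 486.
- With drop-out: 486/0.9 = 540, as stated.

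**2. What was recruited.**
- 254 + 109 = 363, and 363/540 = 67%. The shortfall is 540 − 363 = 177.
- After 10% drop-out: 0.9 × 363 ≈ 327 completers, against 486.
- Intervention plus control over all terms: 523 + 1,090 + 821 + 203 = 2,637. Adding 363 gives 3,000, which matches the abstract's approximate total.

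**3. Power for 0.3 SD.** SE = √(2.77 × (1/n₁ + 1/n₂)) in SD units; normal-formula power = Φ(0.3/SE − 1.96); detectable difference at 80% power = 2.80 × SE.

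| Comparison | Completers | SE | Power (normal) | Detectable difference |
|---|---|---|---|---|
| Equal groups, as in the plan | 327 v 327 | 0.130 | 63% | 0.36 SD |
| Concurrent terms: half of 821 + 203 = 1,024, less 10% | 461 v 327 | 0.120 | 70% | 0.34 SD |
| All terms pooled: half of 2,637, less 10% | 1,187 v 327 | 0.104 | 82% | 0.29 SD |

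**4. Sensitivity.**
- Few schools: 327/60 + 461/60 − 2 ≈ 11 degrees of freedom. A t test then gives 62% on the concurrent set. The pooled set has about 23 degrees of freedom and gives 79%. On the same basis the planned 486 per group gives 74%.
- Intervention share of 45% to 55% of the concurrent children: 68% to 72%.
- All 1,024 concurrent children in the intervention arm (922 completers): just under 80%. So no split reaches 80% under these inputs.
- No drop-out (363 v 512): 75%.
- Smaller clusters: 3,000/59 ≈ 51 per school, about 46 after drop-out. This gives 77% concurrent and 88% pooled.
- Adjustment for the baseline value, which the Analysis plan includes: the article gives no correlation. For assumed correlations of 0.3, 0.4, 0.5 and 0.6, with variance reduced by 1 − r², concurrent power is 74%, 78%, 82% and 88%.

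**The case against.** **Recruitment was ongoing.** Spring 2016 is labelled so. But 109 is given as a baseline count, no later intake is listed, the last follow-up is the 12-month visit of that cohort, and the counts sum to 3,000. The label does not plausibly cover a further 177 children.

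**The analysis set may be wider.** This is the strongest point. The Analysis plan includes all randomised classes and nowhere limits this contrast to the concurrent terms. With every intervention class included, the normal formula gives about 82%. A reader might infer from the shortfall that the trial cannot have 80% power on any reading, and the document does not support that. What stands is narrower: the gain comes from intervention children in terms when no school could be assigned to non-treatment, so that comparison is only partly randomised, and the article does not say which set is meant.

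**The recomputed power depends on assumptions.** It does, and smaller clusters or baseline adjustment would raise it. Any restated figure must carry its assumptions.

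**The calculation is correct and prospective.** A reader might infer that 486/540 is wrong or should be deleted. It reproduces, and the article does not claim that 540 were recruited. Deleting it would hide the gap.

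**The contrast is secondary.** The Sample size section says so, and the Analysis plan already commits to mean differences with 95% confidence intervals. The main comparison, with 2,400 required and 2,637 at baseline, is not touched by this point.

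**Conclusion.** The point holds as a gap between planned and recruited numbers that the article does not acknowledge: 363 children against 540. On the plan's equal-group basis, power for 0.3 SD falls from 80% to about 63%. On the concurrently randomised terms it is about 62% to 70%, with about 0.34 SD detectable. On the pooled, partly non-randomised set it is about 82%, with about 0.29 SD detectable. These figures rest on ICC 0.03, 60 completers per school, 10% drop-out, an assumed half share of intervention children and, for the 62%, an assumed 11 degrees of freedom. The shortfall itself rests on none of them. The consequence is confined to a secondary contrast and to how its result will be read.

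**What to change.** - Keep 486 completers and 540 recruited as the planned size, and state beside them that 363 children were recruited.
- State whether the contrast uses only intervention classes from spring 2015 and spring 2016 or those from all terms. If all terms are used, say that part of the comparison is not concurrently randomised.
- Restate power and detectable difference for the chosen set, with the assumptions listed: about 62% to 70% and 0.34 SD concurrent, or about 82% and 0.29 SD pooled. Note that smaller clusters or baseline adjustment would improve both.
- Reword the abstract's primary aim to agree with the Sample size section on the standing of this contrast.
- While editing, reconcile the two-arm terms: the Randomization procedure names autumn 2015, whereas the Data collection timeline lists autumn 2014. This does not change the total of 363.

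The cost is a few sentences and, on the concurrent set, a less favourable power figure. No enrolment, conduct or estimation method changes; the only analysis decision is which intervention classes enter this contrast.
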